### 2.3 Sample size calculation

#### 2.3.1 Sample size calculation of the exploratory phase.

As mentioned above, no data exists about the effect of dapagliflozin on the oxalate and calcium 24-hour urine excretion. Given the observed decrease in urolithiasis event rates in previous studies [68,69] and findings from a rat model investigating the impact of SGLT-2 inhibitors on urolithiasis [69] we anticipate a 10%-50% reduction in 24-hour urinary excretion of oxalate and calcium compared to placebo. This expectation is supported by evidence suggesting that a 10% decrease in urinary excretion of calcium and oxalate is linked to a significant 8% reduction in the risk of recurrence [76]. We, therefore, expect a) the effect size of dapagliflozin to be a reduction of urinary excretion of lithogenic molecules between 15% and 25% reduction and b) subsequently to have a clinically relevant potential to lower the risk of urolithiasis reoccurrence.

The sample size calculation is based on our primary outcomes of the intraindividual comparisons. The sample size calculation based on a paired t-test was performed using G*Power Version 3.1.9.4. The significance level of two-sided testing was set to 0.025 to acknowledge the two primary endpoints [80]. We set the power to 90% and the alpha error to 5%. Due to no comparable data, we assume a standard deviation of 20% and a correlation between the intraindividual comparisons of 0.1. Based on the sample size models in Table 1. (assumed effect size of 25%, correlation between the groups of 0.1) we proclaim a group size of 18 participants plus an expected dropout rate of 4 so a total of 22 participants is reasonable.

**Table 1 pone.0322034.t001:** potential group size calculations based on earlier findings.

Mean difference	Mean ± SD group 1	Mean ± SD group 2	Group size	Group size + 20% dropout
10%	1.0 ± 0.2	1.1 ± 0.22	86	104
15%	1.0 ± 0.2	1.15 ± 0.23	42	51
20%	1.0 ± 0.2	1.2 ± 0.24	26	32
25%	1.0 ± 0.2	1.25 ± 0.25	18	22
30%	1.0 ± 0.2	1.3 ± 0.26	14	17

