#### 2.6.2 Main trial phase.

The main trial will start with wash-out phase I. All patients will receive blood- and 24-hour-urine screenings in week 6 (respectively week 12 overall) to get baseline data. In preparation for the treatment phase I all participants will receive a daily oral placebo administration over the whole period and will be randomized in two groups.

In week 13 the treatment phase I will start and group 1 will receive oral therapy with 10mg of dapagliflozin while group 2 will get an oral placebo administration daily; the treatment response will be evaluated by blood- and urine test after 4 weeks of therapy (respectively week 16 overall) and in the beginning of in washout phase II (respectively week 21 overall). The same test as before will be performed after 6 weeks (respectively week 26 overall) to gain baseline data for treatment phase II. In preparation for the treatment phase II, all participants will receive a daily oral placebo administration. will receive a daily oral placebo administration.

In the end, we will perform treatment phase II with an oral administration of 10mg of dapagliflozin for group 2 and daily placebos for group 1. The treatment response will be evaluated by blood- and urine tests after 4 weeks of therapy (respectively week 30 overall). Finally, the same tests as before will be performed in wash-out phase III in weeks 1 and 6 (respectively weeks 35 and 40 overall). This way we will get data of the non-therapy periods and of the outcome that will be caused by the dapagliflozin therapy. For each patient, a comparison will be made between the excretion of the electrolytes and molecules of the primary and secondary endpoints under dapagliflozin therapy vs. oral placebo administration.

Throughout the whole study procedure, all participants will be advised to follow dietary instructions as recommended in the urolithiasis guidelines of 2023 [62]. The requested measures will include a balanced diet including a high ratio of vegetables and fibers, a low-fat diet, a calcium intake of about 1.0 to 1.2g per day, a reduced intake of salt up to a maximum of 4.0 to 5.0g per day and an intake of animal proteins of 0.8 to 1.0g per kg per day may reduce stone development risk. Furthermore, patients are strongly advised to not lose or gain weight tremendously throughout the trial process so that the date will be comparable over the whole trial period.

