#### 2.7.2 Study discontinuation and management of serious adverse events (SAEs).

The study will be discontinued for any participant in the event of a serious adverse event (SAE), significant protocol deviations, or if continuation poses a risk to the participant’s health. Study discontinuation may also occur at the request of the participant or their treating physician. Criteria for discontinuing a participant’s involvement in the study include:

Occurrence of any SAE related to dapagliflozin or placebo that is life-threatening, results in hospitalization, or causes significant disability (diabetic ketoacidosis, severe urinary and genital infections, hypotension, acute kidney injury, fractures, and hypoglycemia).Persistent non-compliance with the study protocol, such as failure to attend required study visits or adhere to the treatment regimen.Development of any new medical condition or complication that contraindicates continued participation, such as a significant decline in renal function (eGFR <15 ml/min/1.73 m²) or other serious medical conditions requiring immediate treatment outside the scope of the study.At the participant’s request, for any reason, or if the participant becomes pregnant during the study period.

In the event of an SAE, immediate steps will be taken to ensure the participant’s safety, including withdrawal from the study treatment if necessary. All SAEs will be reported to the Institutional Review Board (IRB) within 24 hours of awareness, followed by a detailed report within seven days. If necessary, the IRB can recommend study suspension or termination depending on the frequency and severity of the events.

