## 3. Statistics

### 3.1 Statistical analysis

We plan to perform statistical analysis conforming to the standard methodology. Categorized data will be presented as absolute count and relative frequencies. Continuous data will be reported as mean and standard deviation in case of normal distribution and as median and inter-quartile range (IQR) in case of a non-normal distribution. Two-sided tests are considered to be significant with a p-value <0.05.

Analyses of continuous variables will be performed using parametric and non-parametric tests (paired t-test/ Mann-Whitney-U-test). The primary endpoint is confirmatory and is the reduction of oxalate in the Verum vs. Placebophase, i.e., Dapaglifozine vs. placebo which will be compared with a two sided-t-test. Intergroup comparisons (Dapaglifozine vs placebo) will be performed by an ANOVA for a crossover design on the group of patients who went through all trial phases and corrected with Bonferroni post-hoc Tests for multiple testing. Frequencies of urolithiasis will be tested with the x²-test, a in comparison of both treatments by the McNemar-Test. Correlations between variables will be performed using Pearson or Spearman coefficients.

Findings will be corrected for multiple testing using the Tukey method if the statistical analysis is performed with a one-way ANOVA or with the Shaffer correction if the statistical analysis is performed with a Kruskal-Wallis test. All other statistical tests will be corrected using the Bonferroni-Holm method.

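### The crossover ANOVA is confined to patients who completed every phase, and the rank test paired with the paired t-test is one for independent samples

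*Protocol article*

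**What the plan says.** Section 3.1 gives the confirmatory comparison as "Dapaglifozine vs. placebo which will be compared with a two sided-t-test", without an analysis set. It then specifies, for the same contrast, an "ANOVA for a crossover design on the group of patients who went through all trial phases". No analysis of all randomised patients is named. The phases end with wash-out III in week 40, while the sample taken directly after treatment phase II falls in week 35 (Section 2.6.2 and WP8).

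Section 2.3.2 adds 20% to the calculated sample size for dropout. Section 2.7.2 lists the grounds for ending participation. These include treatment-related serious adverse events and "Persistent non-compliance with the study protocol, such as failure to attend required study visits or adhere to the treatment regimen".

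Continuous variables are to be analysed "using parametric and non-parametric tests (paired t-test/ Mann-Whitney-U-test"). The data are within-patient. Section 2.6.2 says "For each patient, a comparison will be made between the excretion of the electrolytes and molecules of the primary and secondary endpoints" under drug and under placebo, and Section 2.3.1 says "The sample size calculation based on a paired t-test was performed using G*Power Version 3.1.9.4".

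**The concern.** There are two separate problems in Section 3.1.

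First, whether a patient goes through all phases is known only after randomisation. Adverse events, loss of tolerance and poor adherence can depend on which treatment was taken and in which period. Restricting the comparison to completers makes it a comparison among patients who tolerated and adhered to both sequences of treatment, and tolerance is itself a secondary endpoint. With a fifth added for dropout, the plan expects this loss. Read literally, the rule also removes a patient with both treatment periods fully measured who misses only the week-40 visit.

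Second, Mann-Whitney U treats the two measurements of one patient as coming from different patients. With positive within-patient correlation it overstates the variance of the difference. The test becomes conservative and gives up part of the gain for which a crossover is chosen. Section 3.1 itself expects that some variables will not be normally distributed, so this fallback may well be used.

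**Working it through.** **1. The plan's own figure.** Inputs from Section 2.3.1 and Table 1: means 1.0 and 1.25, SDs 0.20 and 0.25, correlation r = 0.1, power 90%.

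- SD of the difference = √(0.20² + 0.25² − 2 × 0.1 × 0.20 × 0.25) = √0.0925 = 0.304
- Standardised difference = 0.25 / 0.304 = 0.822
- Paired t-test (noncentral t), two-sided 0.05: n = 18, as stated

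The same method at two-sided 0.05 returns every row of Table 1 (86, 42, 26, 18, 14). The planning therefore rests on within-patient differences. Section 2.3.1 also says "The significance level of two-sided testing was set to 0.025 to acknowledge the two primary endpoints". That level would give 21 rather than 18, which is a separate matter. The checks below use 0.05, the level in Section 3.1 and the one that reproduces Table 1.

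**2. How many patients the completers rule could remove.** The abstract gives 17 to 104 as the possible size of the main trial, which is the span of Table 1. If the planned dropout occurs:

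| Table 1 row | Needed | With margin | Left out | Share |
|---|---|---|---|---|
| 10% | 86 | 104 | 18 | 17% |
| 15% | 42 | 51 | 9 | 18% |
| 20% | 26 | 32 | 6 | 19% |
| 25% | 18 | 22 | 4 | 18% |
| 30% | 14 | 17 | 3 | 18% |

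**3. What that can do to the estimate.** If a share p is left out and the mean effect in those patients differs from the completers' by δ, the completers' estimate differs from the all-randomised mean by p × δ. With p = 4/22 = 0.18 and an assumed δ of 0 to 25 points in the unfavourable direction, a completers' effect of 25% corresponds to an all-randomised effect between 25% and (18 × 25 + 4 × 0) / 22 = 20.5%. The document gives no value or sign for δ, so this shows scale only. A δ of the opposite sign would move the figure upwards.

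**4. Precision lost by dropping incomplete patients.** Assume 18 completers split evenly between sequences, 4 patients with period 1 only (two per sequence), and a common SD σ.

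- Information on the treatment effect from completers = 18 / [2σ²(1 − r)]: 10/σ² at r = 0.1 and 18/σ² at r = 0.5
- Information from period-1-only patients = 1 / [σ²(1/2 + 1/2)] = 1/σ²
- Variance with all patients relative to completers: 10/11 = 0.909 at r = 0.1; 18/19 = 0.947 at r = 0.5

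Dropping these patients raises the variance by about 10% and 6% respectively.

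**5. Mann-Whitney against signed-rank.** Bivariate normal pairs, two-sided 0.05, 10,000 runs per cell, using Table 1's own combinations of size and effect with their SDs. The null runs keep those SDs and set the mean difference to zero. Only r = 0.1 comes from the document; 0.5 and 0.7 are assumptions.

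| Pairs, effect | r | Mann-Whitney power | Signed-rank power | Mann-Whitney true type I error |
|---|---|---|---|---|
| 18, 25% | 0.1 | 88% | 89% | 3.9% |
| 18, 25% | 0.5 | 94% | 99% | 0.9% |
| 18, 25% | 0.7 | 97% | 100% | 0.2% |
| 42, 15% | 0.1 | 88% | 89% | 4.0% |
| 42, 15% | 0.5 | 93% | 99% | 0.9% |
| 42, 15% | 0.7 | 97% | 100% | 0.1% |

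The signed-rank test held its level at 4.8% to 5.0%. A separate simulation gave 3.6% and 1% for Mann-Whitney at r = 0.1 and 0.5, which agrees closely. At two-sided 0.025 with 18 pairs and a 25% difference (3,000 runs), power was 81.0% against 82.2% at r = 0.1 and 86.5% against 97.4% at r = 0.5.

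**The case against.** Much of Section 3.1 is sound, and several stronger readings that a reader might reach are not supported.

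- **That the analysis as a whole discards pairing.** It does not. The paired t-test, the crossover ANOVA and the McNemar test all keep it, and only the rank-test fallback is affected. Mann-Whitney would even be valid if applied to within-patient period differences compared between the two sequences. The text does not say this; it lists the test as the partner of the paired t-test.
- **That stone frequency is compared between treatments by an independent-samples test.** The sentence beginning "Frequencies of urolithiasis will be tested with the x²-test" goes on to assign McNemar to the treatment comparison.
- **That one-way ANOVA or Kruskal-Wallis is used for the treatment contrast.** Both appear only conditionally, in the sentence on multiplicity correction.
- **That period effects are ignored.** A crossover ANOVA ordinarily has a period term, and the exact model can be left to an analysis plan.
- **That Mann-Whitney costs 26 to 42 points of power.** Such losses (51% against 77% or 93%) arise only if 18 pairs are combined with a 15% effect and r of 0.5 or 0.7. Table 1 assigns 42 pairs to that effect.
- **That the confirmatory result is certainly a completers' result, or is biased in favour of the drug.** The restriction is written for the ANOVA, and the t-test states no set. A paired t-test would nonetheless need both periods. The direction of bias is not determinable.

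It is also fair to say that the week-40 exclusion is a literal reading rather than a stated rule, that 22 is the size of the single-arm exploratory phase, and that the precision gained from incomplete patients is modest. What stands is that both choices are stated in the article, so they are not details left to an unseen analysis plan.

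**Conclusion.** The concern holds in a limited form. The crossover ANOVA is restricted to a set defined after randomisation, with no all-randomised analysis beside it, in a trial that plans for 20% dropout and whose discontinuation grounds can be related to treatment. Up to 17% to 19% of enrolled patients could be left out if the planned dropout occurs. The resulting bias cannot be sized or signed from the document.

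The rank test named for paired data is the wrong one unless it is applied to period differences. The error is conservative, so it adds no false-positive risk. At the plan's r = 0.1 the loss of power is about 1 point. At assumed correlations of 0.5 to 0.7 it is 3 to 6 points for Table 1's own size and effect pairings at two-sided 0.05. Section 2.3.1 says r = 0.1 was assumed for lack of comparable data, so a higher correlation cannot be ruled out. The power figures assume normal data. This should be corrected, but it does not invalidate the design.

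**What to change.** In Section 3.1, define the main analysis set as all randomised patients with at least one on-treatment oxalate value. Analyse it with a mixed model containing treatment, period, sequence and a random patient effect. State that the confirmatory comparison uses this set, and keep the completers' ANOVA as a sensitivity analysis. Replace Mann-Whitney U by the Wilcoxon signed-rank test, or state that the rank-sum test is applied to within-patient period differences between the two sequences.

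The cost is a change of wording and slightly more analysis work, with no new data. The mixed model relies on data being missing at random, and this assumption should be stated. The model does not remove bias if dropout depends on unobserved oxalate values.

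### The confirmatory oxalate comparison has no single decision rule: the analysis and sizing sections give conflicting alpha levels and corrections, and a literal Holm reading would not deliver 90% power

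*Protocol article*

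**What the plan says.** Four statements in the protocol article bear on the significance level of the main trial's primary comparison.

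- **Section 3.1, general threshold:** "Two-sided tests are considered to be significant with a p-value <0.05". The primary is called confirmatory and is described as "Dapaglifozine vs. placebo which will be compared with a two sided-t-test".
- **Section 3.1, crossover ANOVA:** the comparison of dapagliflozin with placebo in patients who completed all phases is "corrected with Bonferroni post-hoc Tests for multiple testing".
- **Section 3.1, last paragraph:** findings are adjusted "using the Tukey method if the statistical analysis is performed with a one-way ANOVA or with the Shaffer correction" where a Kruskal-Wallis test is used. The paragraph closes with "All other statistical tests will be corrected using the Bonferroni-Holm method". It names no family and does not exempt the primary.
- **Sections 2.3.1 and 2.3.2, sizing:** "The significance level of two-sided testing was set to 0.025 to acknowledge the two primary endpoints". Section 2.3.1 then also gives an alpha error of 5%. Section 2.3.2 lists a significance level of 0.025 and an alpha error of 5% together for the main trial.

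Section 2.5.3 names one primary endpoint for the main trial, oxalate excretion. Section 2.5.4 lists calcium as secondary. Section 2.3.2 leaves the main-trial size to be recalculated from exploratory-phase data.

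**The concern.** The trial has one confirmatory test, and its verdict should not depend on which sentence of the plan a reader applies. As written it does. A p-value of 0.03 is significant under the general threshold, not significant at the 0.025 used for sizing, and not significant at the first step of a Holm procedure over nine or ten tests.

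The second consequence is for power. A t-test is neither a one-way ANOVA nor a Kruskal-Wallis test, so the closing Holm sentence literally covers the primary. If it is applied that way, the primary may have to pass a much stricter level than either 0.05 or 0.025. The recalculated main-trial size would then fall short of its 90% target.

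There is a lesser and separate defect. Tukey and Shaffer are tied to tests for independent groups. No analysis listed in the article is assigned to either test, and neither suits a two-treatment crossover within patients.

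**Working it through.** **Inputs.** From section 2.3.1 and Table 1, 25% row: means 1.0 and 1.25, SDs 0.2 and 0.25, correlation 0.1, paired t-test, 90% power, group size 18 (22 with dropout). From section 2.5.4: eight secondary items. The number of tests, m, is an assumption, because the article defines no family. One test per item plus the primary gives m = 9, and adding stone frequency gives m = 10. Metabolomics could make it larger.

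**Effect size.** SD of differences = √(0.2² + 0.25² − 2 × 0.1 × 0.2 × 0.25) = √0.0925 = 0.304. Standardised difference dz = 0.25 / 0.304 = 0.822.

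**Reproducing Table 1** (exact paired t-test power from the noncentral t distribution, 90% power, each row with its own SDs):

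| Mean difference | Printed n | n at two-sided 0.05 | n at two-sided 0.025 |
|---|---|---|---|
| 10% | 86 | 86 | 102 |
| 15% | 42 | 42 | 49 |
| 20% | 26 | 26 | 30 |
| 25% | 18 | 18 | 21 |
| 30% | 14 | 14 | 17 |

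All five rows match at 0.05 and none matches at 0.025. The text states an allowance for two tests, but the printed sizes contain none.

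**Power of the primary in the 25% row.** The noncentrality is dz × √n, which is 3.49 at n = 18 and 3.77 at n = 21.

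| Level applied to the primary | Power, n = 18 | Power, n = 21 | n for 90% |
|---|---|---|---|
| 0.05 | 90.7% | 94.7% | 18 |
| 0.025 | 83.7% | 90.0% | 21 |
| 0.05/9 = 0.0056 | 62.5% | 73.5% | 29 |
| 0.05/10 = 0.0050 | 60.9% | 72.1% | 29 |
| 0.05/20 = 0.0025 | 50.0% | 62.3% | 33 |

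**Allowing for Holm's steps.** Holm is step-down, so 0.05/m is the strictest level the primary could face. Simulated Holm power for the primary (independent tests, 100,000 runs, each true secondary effect as large as the primary's):

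| Secondaries with an effect | n = 18, m = 9 | n = 18, m = 10 | n = 21, m = 9 | n = 21, m = 10 |
|---|---|---|---|---|
| None | 63% | 61% | 74% | 72% |
| About half (4 of 8, 5 of 9) | 68% | 67% | 79% | 79% |
| All | 80% | 79% | 90% | 90% |

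At n = 18 every scenario falls short of 90%. At n = 21 the target is met only if all secondaries have effects as large as the primary's.

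**The case against.** The strongest reply is that the Holm sentence was never meant for the primary. Section 3.1 calls that test confirmatory, gives it its own procedure and states a 0.05 threshold. The Holm sentence closes a separate paragraph and can be read as covering the remaining tests. Defining families is often left to a full protocol or analysis plan, and over-correction would not inflate the type I error. This reply stands to the extent that a reader might infer that the plan places the primary in one family with every secondary. The article does not say so. It does not answer the inconsistency, because the article itself sets these rules and they disagree.

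Three other stronger readings are also unsupported:

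- **That the sizing made no allowance for multiplicity at all.** Sections 2.3.1 and 2.3.2 state 0.025, which allows for two tests. Table 1 was computed without it, and neither level covers nine or more tests.
- **That the main trial will run at n = 18 with 63% power.** Eighteen is the size of the exploratory phase, a single group without placebo. The main-trial size is still open.
- **That the Tukey and Shaffer rules cost the primary power.** They are conditional on tests that no listed analysis uses, so they cannot affect it.

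Finally, an ANOVA over several time points might legitimately need post-hoc comparisons. The Bonferroni clause therefore need not be deleted outright. It simply has nothing to adjust in a single contrast between two treatments.

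**Conclusion.** The point holds as an inconsistency in the decision rule for the only confirmatory test. Section 3.1 offers 0.05, Holm without a family, and a Bonferroni correction of the same treatment comparison. The sizing sections offer 0.025 beside 5%, with a two-endpoint rationale that does not fit a main trial with one primary endpoint.

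The power loss is conditional on applying the Holm sentence literally. With the 25% row, the printed SDs, a correlation of 0.1 and an assumed 9 to 10 tests, worst-case power is 61-63% at n = 18 and 72-74% at n = 21. These figures illustrate the problem and are not forecasts for the main trial, because the recalculation could still use the right level. This should be corrected before that recalculation, which needs one unambiguous alpha.

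**What to change.** 1. In section 3.1, state that the single oxalate contrast between dapagliflozin and placebo is tested once, outside any multiplicity correction, at one named two-sided alpha. With one primary endpoint, 0.05 is the natural choice.
2. Use the same figure in section 2.3.2 and in the recalculation, and remove the double statement of 0.025 and 5%. If 0.025 is kept instead, compute the size at 0.025: the 25% row then needs 21 evaluable patients, not 18. With the plan's own 20% addition that is 21 × 1.2 = 25.2, so 26 instead of 22.
3. Limit Holm to the listed secondary endpoints.
4. Separately, remove the Tukey and Shaffer sentence, and state that the Bonferroni post-hoc clause does not apply to the single treatment contrast.

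The cost is a few sentences in sections 2.3.2 and 3.1. At 0.05 the printed Table 1 sizes need no extra patients. At 0.025 the 25% row needs three more evaluable patients.
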